## Abstract

**Background:**

Palliative care (PC) is a new concept in Iraq, and there is no training for health care specialists or the public. The lack of education and training programs is the most important barrier for PC. Intermediate training is needed for nurses who regularly manage patients with life-threatening diseases. The End-of-Life Nursing Education Consortium for pediatric palliative care (PPC) program is intended for nurses who are interested in providing care to children with life-limiting diseases or providing support in the event of an accident or unexpected death.

**Objective:**

Our trial aims to evaluate the effect of a web-based training course, using the Normalization Process Theory. It focuses on how complex interventions become routinely embedded in practice and on training of a sample of academic nurses in the application of PPC in routine daily practice. It hypothesizes that nurses will be able to provide PC for the pediatric population after completing the training.

**Methods:**

This is a multicenter, parallel, pragmatic trial in 5 health care settings spread across a single city in Babylon Province, Iraq. Participants will be recruited and stratified into 2 categories (critical care units and noncritical care units). In the experimental condition, 86 nurses will be trained in the application of PPC for 2 weeks through a web-based training course powered by the Relais Platform. The nurses will be invited to participate via email or instant messaging (WhatsApp, Telegram, or Viber). They will provide end-of-life care in addition to usual care to children and adolescents with life-limiting conditions. In the control condition, 86 nurses will continue usual care. The program’s effectiveness will be assessed at the level of nurses only. We will compare baseline findings (before the intervention) with postintervention findings (after completing the training course). A further assessment will be performed 3 months after the course. As numerous unidentified factors can influence the effect of the training, we will perform a progressive evaluation to assess sample selection, application, and intervention value, as well as implementation difficulties. The nursing staff will not be blinded to the intervention, but will be blinded to the results.

**Results:**

The study trial recruitment opened in July 2020. The first outcomes became available in December 2020.

**Conclusions:**

The trial attempts to clarify the delivery of PC at the end of life through the implementation of a web-based training course among Iraqi nurses in the pediatric field. The study strengths include the usual practice setting, staff training, readiness of staff to participate in the study, and random allocation to the intervention. However, participants may drop out after being transferred to another department during the study period.

**Trial Registration:**

ClinicalTrials.gov NCT04461561; https://clinicaltrials.gov/ct2/show/NCT04461561

**International Registered Report Identifier (IRRID):**

PRR1-10.2196/23783

## Introduction

### Background

Pediatric palliative care (PPC) involves comprehensive active care for children and young adults, and is a globally recognized priority in caring for those with life-limiting conditions. This recognition was justified by high rates of mortality from cancer specifically. Therefore, skilled and supportive care, pain management, and symptom control at the end of life have been approved in palliative care (PC) [1,2].

Annually, 7 million families could benefit from PPC, but those in low- and middle-income countries seldom have such access, and there are approximately 1.2 million children globally, with more males than females. These children desperately need this type of care, and they eventually die from multiple and varied problems, such as birth defects, malnutrition-related diseases, meningitis, AIDS, and cardiovascular diseases [3].

Overall, in 2011, more than 29 million individuals from diverse age groups died from diseases demanding PC, with the largest proportion being adults rather than children less than 15 years old. Globally, each year, only 63 children out of 100,000 children less than 15 years old require PC at the end of life [3].

The World Health Organization presents PC as an integrated approach involving rules, opioid availability, facility obtainability, and educational platforms, as well as PC-certified activities, and it is available in 15 Eastern Mediterranean countries. Saudi Arabia has the maximum number of PC agendas, in addition to Iran and Lebanon, who award official licensing for their physicians, followed by Egypt and Jordan. Moreover, Oman, Jordan, Egypt, and Qatar have established other advanced programs for training (eg, master’s degree or diploma). However, Iraq and occupied Palestinian areas have not started such care [4].

Some physicians and nurses have attended essential and advanced workshops on PC since 2011, but it is still considered a new concept in Iraq, with no formal policies or guidelines relating to this field, and the main contributors for introducing PC are nongovernmental organizations and the Middle East Cancer Consortium [4,5]. The number of qualified doctors is very low in Iraq, as trained physicians are fleeing the country owing to political instability. There are no degree programs in palliative medicine in Iraq, and a quarter of nurses are college graduates, with most lacking primary education [5]. No actual policy changes have been made in the previous 10 years. In the last 6 years, new opioids have been introduced, but they are not permissible for outpatients and not easily available. Only medics in government hospitals can recommend these opioids, and they are for oncology and not PC. Individual funders have started appealing to provide support for oral morphine if permitted by the Ministry of Health. There is no instant morphine or continued-release morphine. Injectable morphine, codeine, and transdermal fentanyl patches became available in 2013, which are obtained for free, and upgrading these drugs has been deliberated [4].

Obstacles to PC can be divided into the following 3 parts: (1) deficit of health policies in the sustenance of PC improvement; (2) nonexistence of significantly trained health care workers; and (3) reduced accessibility to essential PC drugs [6,7]. All these obstacles can be overcome by addressing the important barriers that are delaying PC development in Iraq, namely, lack of public responsiveness, lack of education, lack of training programs, inadequate opioid accessibility, and no identification of PC as a field [3,4].

The political state and uncertainty in the nation have played main roles in postponing the awareness of the public. Furthermore, the greatest pediatric care providers consider that PC is a good means to disclose that more cannot be done [4].

Regarding the present PC condition in many countries in the Middle East, there is a need for emphasis on the teaching of professional staff members and the presence of a consistent renewed expert committee that would be accountable for the development of the modern PC team [8-10].

PC education needs to be provided in English and is desired at the following 3 levels: (1) basic PC preparation for all health professionals; (2) intermediate training for those consistently working with patients having life-threatening illnesses; and (3) professional PC training for managing patients with more than routine symptom management needs [3].

Without appropriate end-of-life education, it is incredibly difficult for nurses to provide adequate care for related issues. Moreover, it is vital to balance education with attention to personal understanding and attitudes toward death and dying to provide students with opportunities to become knowledgeable about death and grief in order to deal with their feelings and to develop further [11]. From 1997 to 2000, there was a lack of overall nursing content related to end-of-life care and limited end-of-life content knowledge among nursing faculty [12,13]. Efforts are needed, including the development and dissemination of new educational recommendations, training materials, and educational requirements, at both the medical school and residency levels, as well as for nursing students and other health professionals, which should address the need for PC education [14].

To detect and address the limited knowledge of end-of-life care, researchers at the City of Hope National Medical Center in the United States conducted a 3-year project titled “Strengthening Nursing Education to Improve End-of-Life Care,” which was supported by The Robert Wood Johnson Foundation. The project brought together professional nursing organizations, expert clinicians, and educators in palliative/hospice care to improve the curriculum in order to enhance nursing care at the end of life. The project revealed chief insufficiencies in nursing education and its role in end-of-life care, and identified a lack of content in nursing text, insignificant content in the nursing curriculum, insufficient nursing faculty knowledge, and many other educational barriers that inhibit good nursing practice in this area [15-17].

“The End-of-Life Nursing Education Consortium-PPC (ELNEC-PPC)” project based on original training was intended to study the concern of nurses in providing care for life-threatening illnesses to children or for accidents or sudden death [18]. Perinatal and neonatal PC is one module [19]. The ELNEC-PPC train-the-trainer program is for 2.5 days, and those who complete the program will be able to actively share information and knowledge to other health care workers in clinical practice or nursing students in colleges. The first training module was started in 2003, and 8 nationwide train-the-trainer programs have been conducted with more than 700 nurses attending from varied pediatric locations across the United States and Canada.

Many children dying from life-threatening illnesses, such as congenital malformations, chromosomal abnormalities, accidents, low birth weight, and sudden infant death syndrome (50 out of every 100,000 children), could be provided PC services, but little consideration is given to reducing the suffering faced by children and their families [7,18].

Pediatric nurses are considered more occupied than any other health care professionals, and they have a distinctive opportunity to assess and address the needs of children who feel pain and die suddenly or shortly after birth, or die in utero (perinatal death), as well as the needs of their families. However, these nurses may have little knowledge about the principles of caring for terminally ill children with different conditions at different ages [20,21].

On the other hand, a problem might occur with the introduction of a new approach to supply and consolidate health care in practice, which is extensively adopted in health services, community health practice, and areas of social policy that have important health consequences, such as education, transport, and housing. The UK Medical Research Council’s framework for designing and evaluating complex interventions recommends conducting a process evaluation in order to illuminate inconsistencies between predictable and detected outcomes to understand how context impacts outcomes, and to provide insights to assist implementation [22,23].

Previous reports [24-26] mentioned that a certain problematic translational gap continues to exist between demonstrating the positive impact of a complex health care intervention in a study environment and utilizing this intervention in routine daily practice. The Normalization Process Theory (NPT) [27] and its predecessor, the Normalization Process Model [28,29], provide a framework that conceptually helps in understanding and explaining the dynamic processes that can be encountered through the utilization of complex interventions and technological or organizational innovations.

Previous studies [30,31] specified 4 key analytical domains as nonlinear and mentioned that they cooperate energetically to afford broad enlightenment of implementation processes, which anticipate if participants do not understand, sustain, or consider an intervention valuable or compatible with their current work. The NPT was designed to be applied flexibly, can be used at one or more points in a qualitative study, and has been successfully used. Following the NPT [29,31], the process of implementing a complex intervention can be described and explained by employing the following 4 central theoretical constructs:

Coherence: The process and work of sense-making and comprehending that individuals and organizations perform, which promote or inhibit the embedding of a routine practice.Cognitive participation: The process and work that individuals and organizations perform to enroll people to build relationships in a new practice.Collective action: The work that individuals and organizations perform to enact a new practice. Collective action is primarily labeled as a normalization process model and contains 4 subcomponents (“contextual integration,” “relational integration,” “interactional workability,” and “skill set workability”).Reflexive monitoring: The work inherent to the formal and informal appraisal of a new practice to measure the benefits and drawbacks, which can develop users’ knowledge of the effects of a practice.

The NPT has become a widely used theory for analyzing the implementation of complex interventions and has previously been applied to a wide range of health topics and empirical settings, including chronic health care, maternity care, e-learning, and telemedicine. There have been 8 studies in the eHealth and telehealth care fields and 21 studies in several other health care fields, which entirely concluded that the NPT is a complete and valuable model to drive the process of implementation in the setting of a health facility [31].

A quantitative design in a PC health context has not yet confirmed the validity of the NPT model. The NPT tool Normalization Measure Development (NoMAD) [32] has newly been established for use in quantitative research. Similar to the Conceptual Model of Implementation Research [33], the elements are formulated to feature at application with hindsight. Besides, the customization of the NoMAD tool across several contexts is unclear, and this restricts its practical usage in selected settings. For example, a single element of the NoMAD tool tests whether “sufficient resources are obtainable to maintain the intervention” [32]. Nevertheless, to our knowledge, no NPT studies have concentrated on evaluating a web-based training program in PPC at the end of life for nursing interventions in hospital settings.

Training has been recognized as a key implementation approach for enlightening provider knowledge and skills, with an interest in the use of web-based training methods [34,35]. The indication is accumulating that web-based training can be a working educational instrument aimed at bringing and appraising curricular content through numerous organizations and training levels. With high-speed internet access and the universal presence of computers in homes and clinics, health care professionals can effortlessly access web-based resources regardless of their settings and can access resources at periods that do not overlap with their clinical tasks or responsibilities [36].

The original policy for providing consistent behavioral interventions in a series of situations involves web-based interventions, which provide the ability to access behavioral maintenance at any time, and result in greater confidence and lower cost compared with clinician-delivered interventions and old-fashioned face-to-face training methods [35,37].

Survey and qualitative studies mentioned that end-of-life care research is feasible and ethical, but funding of end-of-life care research is poor [38,39]. Thus, randomized trials of end-of-life care treatments and services are uncommon, and are often limited by poor enrollment, high attrition, unfairness, confusion, and small samples [40,41].

Specifically, pragmatic multicenter randomized controlled trials (RCTs) are recommended for the evaluation of complex health care interventions to enrich enrollment and broadcasting, and increase the external validity of trial results [42]. Nevertheless, pragmatic RCTs are intended to evaluate treatments in real-world (as opposed to idealistic) conditions, directly enlightening decision-making by patients, providers, and health care policymakers [43].

### Comparators

Comparators are often used to decide the work level of an intervention related to a clinically relevant substitute. The choice of the comparator (control group) is always a serious decision in a clinical trial, which has the following major purpose: to allow the differentiation of patient outcomes (for example, changes in symptoms, signs, or other morbidities) triggered by the test treatment from outcomes caused by other factors, such as the natural advancement of the disease, observer or patient potentials, or other treatments. The comparator experience helps identify outcomes when patients do not use the test treatment or when they use a different treatment [44].

The present knowledge regarding the absolute value of anticipated experimental and control interventions is considered as one of the factors that regulate the appropriate choice of a comparator for a trial [45]. The research question type is the main ideal comparator determining factor. Significant comparators are those that involve existing clinical or public health services or facilities (eg, usual care or standard care), other implementations (eg, a firm evidence-based practice intervention by way of a comparator aimed at an intervention that is up to date), and clinically pertinent variations in trial implementation (for instance, similar interventions employing an alternate approach, eg, a face-to-face intervention in studies assessing a telehealth intervention) [46].

The pragmatic model intended for the selection of comparators allows investigators to choose clinically important comparators instead of nonnatural comparators that are unlikely to continually be used in clinical practice. The pragmatic model provides a way to resolve the numerous incongruities and influences related to comparators that are used in intervention trials [46].

For this trial, typical care is the comparator of choice, which is considered as a treatment or service that is consistently used, and it is provided after experimental members have joined. It often differs across individuals and settings, and in some trials, it may be increased or decreased for trial participants [46]. According to a previous report [47], customary care is the favorite comparator among researchers. It has been substituted as a comparator or has been a constituent of the comparator in 99 (49.5%) studies, and often appears under numerous synonymous terms (eg, standard treatment, care, as usual, standard care, treatment as usual, and standard of care). However, a previous report [48] stated that it may vary considerably between centers and countries confounding comparator choice. Using clinical guidelines to define usual care can help standardize comparator treatments; conversely, this may decrease the applicability of the results to actual settings.

Hereafter, the selection of typical care for this trial follows Clinical Practice Guideline recommendations, as well as the organized appraisal of significant literature that appears to be related to PC services, which are not accessible to pediatric patients in Iraq owing to deficiency of knowledge and training among health care professionals or limited care supply [4,10,45]. The trial aims to explain the provision of PC at the end of life through the implementation of the ELNEC course as a web-based training program, using the NPT. Its emphasis is on the complexity of interventions, which are routinely embedded in practice. In addition, the trial aims to identify the changes implemented by participant nurses in their clinical practice after participating in the web-based training program to provide PC alongside usual care (intervention group) versus usual care only (control group) for children with life-limiting conditions or in the case of accidents or sudden death at the end of life. Finally, we want to provide findings that will assist in the interpretation of the trial results.

### Objectives

#### Primary Objective

The primary objectives are as follows: (1) to hold a short ELNEC-PPC web-based training program at selected Hillah city hospitals in Iraq by July 2020, and (2) to evaluate the impact and effectiveness of this project through the NPT at the beginning of the web-based training course, and 2 weeks and 3 months after the end of the web-based training course, define PC advocacy activities, and implement the principles found in the ELNEC-PPC web-based training program at selected Hillah city hospitals in Iraq by August 2020.

#### Secondary Objective

The secondary objective is to monitor participants for 3 months after the web-based training program in an attempt to raise their PPC knowledge to improve their self-efficacy levels and attitudes toward PPC at selected Hillah city hospitals in Iraq by August 2020.

## Methods

### Trial Design

This study is designed as a multicenter, investigator-blinded, parallel, 3-month, pragmatic, 2-arm, superiority (provision of PPC with usual care is superior to usual care only) RCT, in which different units from multiple hospitals are stratified and randomized. Randomization will be performed as block randomization with 1:1 allocation, and it will be conducted according to the Consolidated Standards of Reporting Trials (CONSORT) guidelines. The CONSORT statement is a guideline designed to improve the transparency and quality of the reporting of randomized trials [49,50].

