### Randomization

Participants will be randomized to either (1) ELNEC-PPC web-based training as well as usual care or (2) only usual care. The randomization involves block randomization plus permuted blocks of random size known to the researcher and stratified by the type of unit (ie, critical care unit and noncritical care unit). The allocation ratio between the intervention and control groups is 1:1. Randomization will be performed using the Sealed Envelope website [53].

Randomization involves generating random numbers using a computer. The numbers are distributed and written on the nomination forms for the training course in the text boxes on the top of the forms. According to the sample size, the first random number represents the intervention group and will be written on the form with the code “T,” and the random number for the control group will be written with the code “C.” The forms are placed in sealed envelopes, and these are mixed and placed in a large sealed envelope (A3) (Multimedia Appendix 8). These steps represent the randomization process performed by a nurse. A video is made of the process of preparing the sealed envelopes, with the participant details visible. A second researcher will later view the video to ensure the accuracy of the process. Corresponding envelopes will be opened only by the participants who select them, and they will be allocated accordingly. The enrolled participants will complete all baseline assessments.

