### Sample Size

The study has been designed as a superiority trial with 2 parallel groups (ELNEC-PPC web-based training plus usual care and usual care only). For calculation of the appropriate sample size, the main researcher uses the assumption that the 5 selected settings have 254 nursing staff members on average eligible for inclusion based on a survey of all included settings before the study to determine the total number of nurses who work in the selected settings and are appropriate for inclusion. Based on this assumption, as well as a 2-sided *P* value <.05, a 0.90 power, a traditional predictable correlation between 2 measurements of 0.5, and an intraclass correlation coefficient with *P*<.05, 86 participants were required in the intervention group and 86 were required in the control group for *t* tests. To support equal sample sizes, including for the units of the selected settings, and to account for intrastratified correlations of units, a multilevel analysis will be used. Nursing staff members who are transferred to a dissimilar organization unit will be exchanged from the sample of nursing staff, and changes will take place in the course of the study. To catch up with nursing staff members who are not changed in time, the researchers will insert an additional organization unit from the critical care units for the intervention and control groups, which will result in a total of 172 nursing staff members. All power analyses will be performed using the G*Power software (version 3.1).

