### Statistical Analysis

Results will be stated according to the CONSORT declaration concerning health [49,50]. The analysis of primary data will follow the intention-to-treat principle and relate the alterations in the overhead outcome measures between the intervention and control groups. SPSS Version 26.0 software (IBM Corp) will be used for the data analysis. Descriptive statistics will be presented by percentage distributions and indicators describing the location (arithmetic mean=M) and deviation (range; standard deviation=SD). The analysis of primary data will predict the mean difference with 95% CI in the NoMAD score at the 3-month follow-up between the intervention and control groups.

The model includes accessible data of nurse participants at all time points (ie, starting point, and after 2 weeks and 3 months). Within the regression model, distinct participants will be considered using a random effect approach, accounting for inside topic covariance construction. The group and time effects will be considered with asset effects using a combined intervention and time variable. Starting point levels will be obtained over 2 research collections supposing that starting point alterations are coincidental [66]. This is aimed at minimal starting point changes in the outcome variable.

Both groups will primarily be labeled according to their starting point features. The initial data will be analyzed to evaluate the effectiveness of ELNEC-PPC web-based training in the intervention group when compared with the findings in the control group, according to the NPT.

The analysis will inspect intervention effects continuously over time, and will assess the interaction between period and group allocation. The difference between the groups will be assessed for the period of the basic model and will be further evaluated according to the stratification by unit category (critical care unit and noncritical care unit) [67].

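### The protocol names two different units of randomization, and its primary model omits the unit and stratum terms that its own sample-size section and design call for

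*Protocol article*

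**What the plan says.** Protocol article, Trial Design: this is a two-arm parallel superiority trial with 1:1 block randomization in which "different units from multiple hospitals are stratified and randomized".

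Protocol article, Randomization: "Participants will be randomized to either (1) ELNEC-PPC web-based training as well as usual care or (2) only usual care". Stratification is by unit category (critical or noncritical care), and the mechanism is one coded form in one envelope per nurse: "Corresponding envelopes will be opened only by the participants who select them, and they will be allocated accordingly".

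Protocol article, Sample Size: 86 nurses per arm for t tests, at two-sided 0.05 and 90% power. The section mentions an intraclass correlation but attaches only a P value to it, not a magnitude. It states that "to account for intrastratified correlations of units, a multilevel analysis will be used". It also plans to bring in a further critical care unit for the two arms to cover staff turnover.

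Protocol article, Statistical Analysis: "Within the regression model, distinct participants will be considered using a random effect approach", together with a joint group-by-time fixed effect and a common baseline. No unit term and no stratum term are named. After the basic model, the group difference "will be further evaluated according to the stratification by unit category". A repeated measures ANOVA is added, also with no unit term named, and the secondary outcomes are to be analysed in a similar way to the primary.

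**The concern.** There are two inconsistencies. The first is what was randomized. Trial Design says units, and the plan to add a whole unit for the arms can be read the same way; Randomization says nurses. The second is the model. Sample Size commits to an analysis with a unit level, and Statistical Analysis describes one without it.

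They matter jointly. The unit of randomization decides whether a participant-only model is valid. If whole units go to one arm, between-unit variation enters the treatment contrast and a model that ignores it understates the standard error. If nurses are allocated individually, it does not. Correlation within units is plausible because 7 of the 20 construct items of the questionnaire concern collective action, which is partly shared by colleagues on a unit. A reader cannot tell from the article which analysis will be reported, or whether the P value from the described model can be taken at face value.

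**Working it through.** **Inputs from the protocol.** Study Setting lists 1+1+1+2+1+1+1+1+1 = 10 critical care units and 1+1+1+1+5 = 9 noncritical ones, 19 in all. Sample Size gives 86 per arm, 172 in total, so the mean is 172/19 = 9.05 nurses per unit. Alpha is 0.05 two-sided, power 0.90, and the correlation between measurements 0.5.

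**Assumed, because not given.** Intraclass correlation (ICC) 0.01 to 0.10; standardized effect d = 0.5; stratum difference 0 to 0.5 SD.

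**The plan's own figure.** No effect size is stated, so 86 cannot be derived from the stated inputs alone. At an assumed d = 0.5, the normal formula gives 85 per arm and the t test gives 85.03, rounded up to 86. A change score with correlation 0.5 has SD = sqrt(2(1 − 0.5)) = 1 and gives the same answer. This uses a design effect of 1.

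**If units were randomized.** Design effect DE = 1 + (9.05 − 1) × ICC. True level of a nominal 0.05 test that ignores units = 2(1 − Φ(1.96/√DE)). Ratio of reported to true standard error = 1/√DE. Power at 86 = Φ(0.5/(√(2/86) × √DE) − 1.96).

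| Assumed ICC | DE | SE ratio | True level | Power at 86 (d = 0.5) | 86 × DE, rounded up |
|---|---|---|---|---|---|
| 0.01 | 1.081 | 0.96 | 0.059 | 0.88 | 93 |
| 0.05 | 1.403 | 0.84 | 0.098 | 0.79 | 121 |
| 0.10 | 1.805 | 0.74 | 0.145 | 0.68 | 156 |

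A simulation of 19 units and 172 nurses at one time point (6,000 replicates per cell) gave rejection rates of 0.055 to 0.061, 0.090 to 0.100 and 0.134 to 0.142 at these three ICCs, close to the formula.

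**If nurses were randomized within the two strata.** The same simulation, again without unit or stratum terms, gave:

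| ICC | Stratum difference (SD) | SE ratio | Type I error |
|---|---|---|---|
| 0 | 0 | 0.999 | 0.052 |
| 0 | 0.5 | 1.026 | 0.043 |
| 0.01 | 0 | 0.990 | 0.051 |
| 0.01 | 0.5 | 1.039 | 0.040 |
| 0.05 | 0 | 1.017 | 0.046 |
| 0.05 | 0.5 | 1.021 | 0.043 |
| 0.10 | 0 | 1.002 | 0.052 |
| 0.10 | 0.5 | 1.025 | 0.043 |

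The Monte Carlo error of each SE ratio is about 1/√(2 × 6,000) = 0.009, so the values without a stratum difference are compatible with 1 or nearly so. The excess comes mainly from the omitted stratum: with two strata of about equal size, a 0.5 SD difference adds about 0.25 × 0.5² = 0.0625 to the error variance, and √1.0625 = 1.03.

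**The case against.** The operational text is consistent about individuals. Codes go on each nomination form, nurses open their own envelopes, and the enrollment section tells each participant the outcome of the allocation. One clause in Trial Design does not outweigh that procedure, so the inflated error rates describe the less likely design. This stands, and it is why the point is one of consistency and efficiency first. It does not remove the contradiction, because the plan to add a whole unit also reads loosely.

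It can also be said that the article is condensed, that it commits to a multilevel analysis, and that the full list of model terms may sit in an analysis plan not shown. This stands in part. A reader might infer that the plan ignores clustering, and the Sample Size section shows that it does not. But the article itself describes the primary model, and that description does not match the commitment.

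A reader might further infer that the standard errors are wrong whichever unit was randomized, for instance by taking 1/√(1 − ICC), which is 1.026 at 0.05 and 1.054 at 0.10, as an error under nurse randomization. That is not supported. Stratification is by unit category, not by unit, so the arms are not balanced within units and the unadjusted standard error properly carries the between-unit variance. The ratio is roughly the most precision that a unit term could gain.

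Finally, the type I error figures are for one time point. The planned model also uses baseline, which would absorb part of any persistent unit effect, so the inflation under unit randomization could be smaller than shown.

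**Conclusion.** The point holds in a conditional form and should be fixed. The article contradicts itself on the unit of randomization, and its primary model does not match the multilevel analysis it promises.

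Under nurse randomization, which the Randomization section describes, the model is valid to slightly conservative: standard error ratio about 1.00 to 1.04 and type I error about 0.040 to 0.052. The cost is some lost precision, mainly from leaving out the stratum. Under unit randomization, the true level would be about 0.06 to 0.145 over assumed ICCs of 0.01 to 0.10, and power at 86 per arm would fall from 0.90 to between 0.88 and 0.68 if d = 0.5.

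The protocol gives no ICC, effect size or stratum difference, so all of these are assumptions. The simulation had no contamination between arms within a unit and no variation of the treatment effect across units. Nor does the figure of 86 prove that clustering was left out. At d = 0.6 a t test needs 59.35 per arm, and 86/59.35 = 1.449 would correspond to an ICC of (1.449 − 1)/8.05 = 0.056. What can be said is that no inflation step or ICC value is visible.

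**What to change.** 1. State one unit of randomization in Trial Design, Randomization and Sample Size, matching what was actually done, since recruitment opened in July 2020. The envelope procedure points to nurses. If the sponsor confirms this, Trial Design should say that nurses are randomized 1:1, stratified by unit category, and Sample Size should make clear that an added unit is a source of further nurses and is not itself allocated.
2. In Statistical Analysis, add unit category as a fixed effect and a random intercept for unit, with nurses nested in units, to the primary mixed model. This delivers what Sample Size promises. Apply the same structure to the secondary outcomes, and say how the repeated measures ANOVA relates to this model.
3. Keep the comparison of effects between critical and noncritical units as a subgroup analysis, separate from the stratum adjustment.
4. If units were in fact randomized, also give the ICC value and the assumed effect size, and restate the power.

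The cost is small: a few sentences and two lines of SPSS mixed-model syntax. The one drawback is an extra variance component that may be estimated as zero, so the plan should say that the model then proceeds without it.
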